## Ethics and dissemination

### Ethics approval and consent to participate

This study protocol and execution of the study will be fully compliant with the most recently updated version of the Declaration of Helsinki. The researchers will protect confidential data in accordance with the rules and regulations stated in the Dutch General Data Protection Regulation. The method for data storage and handling is approved by the data security officer of Máxima MC. The Medical Ethics Committee of Máxima MC extensively reviewed the study protocol and concluded that the study is in line with the Medical Research Involving Human Subjects Act. Therefore, ethical approval was granted (W22.070/NL82869.015.22). Máxima MC Board of Management also approved the conduct of this study at their hospital. Written informed consent will be obtained from all subjects involved in the prospective part of the study and from all the participants who were transferred to/from another hospital and who are part of the retrospective part of the study. The Clinical Trial Centre Maastricht, acting as an independent monitor, has categorised this study as having ‘Negligible’ risk, resulting in a minimum of seven monitoring visits throughout the study.

### Ethics and risk assessment

Only a relatively small possibility of moderate skin irritation or of a minor allergic reaction resulting from abrading the abdominal skin or applying conductive gel can be anticipated for correct application of the NFMS patch. However, there is limited experience with long-term application of the patch. Skin irritation will be reported as an adverse outcome and will be monitored closely during the study. If necessary, a new patch can be placed on a different site on the abdomen or a switch to conventional CTG monitoring can be made. These women will still be part of the study.

### Dissemination

Results of the study will be disseminated in peer-reviewed scientific journals and conference presentations.

## Discussion

The NIEM-O study investigates the effect of continuous antepartum eCTG monitoring compared with conventional intermittent CTG monitoring, in preterm hospitalised high-risk pregnancies, on perinatal and maternal outcome. Our hypothesis is that the novel monitoring technique (eCTG) and its continuous antepartum use may lead to earlier detection of foetal distress and may prevent unnecessary interventions. This might result in improved perinatal and maternal outcomes. It also provides more insight into preterm and continuous antepartum foetal monitoring. This will support consensus and recommendations regarding the interpretation of antepartum foetal monitoring for preterm fetuses.^45 46^ Similarly, limited knowledge exists regarding the utilisation and interpretation of continuous (electrophysiological) foetal monitoring (eCFM) for a prolonged period of time.^47^ The comprehensive nature of this study’s database renders it suitable for future research inquiries and as a reference database.

A similar large-scale clinical study (NIEM-II study) is currently being conducted in the term population, comparing the effect of eCTG with conventional CTG monitoring during labour on various perinatal and maternal outcomes.^48^ Both studies—this NIEM-O study and the NIEM-II study—employ the same CIRSS design, enabling efficient implementation and comparison of eCTG with standard monitoring in routine clinical care across different obstetric populations.

### Study limitations

It is unknown if reference standards for CTG patterns of term fetuses as stated in current literature can be applied to fetuses during the preterm period.^46^ Also, little to no research is available on the use and interpretation of eCFM for a prolonged period of time.^47^ Before study initiation, all clinical staff involved in CTG interpretation will undergo standardised training sessions based on current literature and internal guidelines.^4649^,^53^ Additionally, daily multidisciplinary meetings will be held to discuss CTG traces, fostering consensus and calibration among attending gynaecologists. These procedures will be documented in an SOP. Accurate determination of the foetal condition based on the CTG trace may be subject to inter-observer variability, possibly influencing perinatal outcome.^46^ However, this concerns both the use of conventional intermittent CTG as well as the continuous eCTG monitoring method. The vernix caseosa, a fatty layer covering the fetus between 28 and 32 weeks GA, may dim the foetal cardiac signal and might lead to insufficient data for NI-fECG analysis.^39^ This possible decrease in signal quality might result in a necessity to switch to conventional CTG monitoring. No risks are involved in switching to the conventional system. Signal loss and switch rate will be documented and are part of the secondary objectives of the study. The CIRSS study design deviates from a standard randomised clinical trial, where both treatment arms are randomised to patients. The inclusion rate of patients is expected to be substantially larger than for a randomised controlled trial, since (almost) all women who participate and receive standard care are automatically included. By making use of causal inference approaches for observational studies, we are able to include patients with standard care from the past, reducing the sample size and the number of patients exposed to the study setting. Also, since women receiving standard care are uninformed of new interventions, we believe the current approach more accurately represents normal practice, while putting as little burden on the women and caregiver as possible. To account for potential differences between the historical and prospective cohorts, including changes in clinical practice over time (eg, due to COVID-19), we applied a propensity score adjustment strategy and conducted sensitivity analyses to ensure methodological robustness and reduce bias.

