
## Methods and analysis

The study is a single centre, prospective cohort intervention random sampling study (CIRSS) with historical controls: the NIEM-O study. Pregnant women will be recruited from the Máxima Medical Centre (MMC), a tertiary obstetric care hospital in Veldhoven, the Netherlands. Inclusion starts at the end of 2023, and is expected to take at least 2 years. Pregnant women will be recruited between 23 and 32 gestational age (GA) when they are admitted to the obstetric high care (OHC). The study protocol (version 9) is approved by the Medical Ethics Committee of Máxima MC (W22.070/NL82869.015.22).

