#### Retrospective recruitment

In order to strengthen the comparison of the two groups (continuous eCTG monitoring and conventional intermittent CTG monitoring), additional data from women who received standard treatment (conventional intermittent CTG monitoring) in Máxima MC Veldhoven, the Netherlands in 2014–2019 will be collected retrospectively. Data will be derived from electronic patient records (EPRs).

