### Sample size

A total of 1911 patients (comprised of 511 prospectively included women and 1400 historical controls) would be sufficient to evaluate the primary objective. Incidence of the composite outcome is based on numbers of perinatal morbidity and mortality of MMC from 2019, combined with a literature-based estimation of the simultaneous occurrence of the perinatal comorbidities and mortality.^40^,^43^ Due to the unknown effect of COVID on perinatal and maternal outcomes,^44^ numbers from MMC of 2020–2021 are not included in the sample size calculation. This resulted in a rounded estimated composite outcome of 17%. Based on clinical experience, an effect size of 6% is expected. To detect this effect size with a power of 80% and a type I error of 5%, a group of 511 women will be invited for the prospective cohort. Of these 511 women, 464 women (90.8%) will be in the sampled study arm and 47 women (9.2%) in the non-sampled study arm. Based on clinical experience, an estimation of 80% acceptance rate for data collection in the sampled and non-sampled group was made (resulting in 372 women and 37 women respectively). Among the 372 women who agreed to data collection in the sampled group, it is expected that 90% will accept and receive eCTG monitoring (335 women) and 10% (37 women) will decline eCTG monitoring and therefore receive CTG monitoring. All 37 women in the non-sampled group will receive standard monitoring. For the retrospective cohort, a total of 1400 participants will be included (figure 3). No dropout rate is calculated, due to continuation of the study and sampling until the requested sample size (of both groups) is reached.

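### The propensity score is said to account for practice change since 2014–2019, but it cannot; with 95% of controls historical, about 95% of any era effect enters the eCTG estimate

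*Protocol article*

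**What the plan says.** Under Retrospective recruitment, standard-care data from Máxima MC, "the Netherlands in 2014–2019 will be collected retrospectively". The Sample size section sets their number: "For the retrospective cohort, a total of 1400 participants will be included". For the prospective part, "Inclusion starts at the end of 2023, and is expected to take at least 2 years" (Methods and analysis).

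Of 511 invited women, "464 women (90.8%) will be in the sampled study arm and 47 women (9.2%) in the non-sampled study arm". After the assumed acceptance rates, 335 women receive eCTG, 37 sampled women decline it and receive CTG, and 37 non-sampled women receive CTG.

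The Statistical analysis section gives the propensity score two tasks. One is to correct for selection among women offered eCTG who receive CTG. The other is to correct for the mix of retrospective and prospective data. The covariates given as examples are maternal (such as age and BMI), foetal (such as gestational age and Dopplers) and care-related (indication, medication use, length of stay). Study limitations extends the claim to practice change: "including changes in clinical practice over time (eg, due to COVID-19), we applied a propensity score adjustment strategy", with sensitivity analyses added. The analyses named in this context under Statistical analysis are the separate components of the composite and subgroups such as obesity.

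Study limitations also says that before the study starts "all clinical staff involved in CTG interpretation will undergo standardised training sessions", and that daily multidisciplinary meetings will discuss traces.

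**The concern.** Every eCTG woman belongs to the new era and nearly every control to the old one, so era and treatment are almost the same variable. If the composite risk changed between 2014–2019 and the enrolment period for any reason other than eCTG, women with identical covariates would have different risks in the two eras. A score on those covariates leaves that difference in the treatment estimate.

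The article itself supplies candidate causes. Training reaches everyone who interprets CTG, daily trace meetings are planned, and Study limitations accepts that variability in reading traces may influence perinatal outcome. A fall in risk would be credited to eCTG, and a rise would hide a real benefit. A reader who relies on the article's statement would think this had been dealt with.

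**Working it through.** **Inputs (Sample size section):** 1,400 historical CTG women; 37 + 37 = 74 concurrent CTG women; 335 eCTG women; control risk 17%; effect 6%, read as absolute (17% v 11%); power 80%; type I error 5%, read as two-sided. These two readings reproduce the stated power.

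**Method.** Normal-approximation test of two proportions, with n1 = 335 at risk p1 and n2 = 1,474 at risk p2. Let d = p2 − p1, and let p̄ be the pooled risk.
- SE0 = √[p̄(1−p̄)(1/n1 + 1/n2)]
- SE1 = √[p1(1−p1)/n1 + p2(1−p2)/n2]
- P(significant in favour of eCTG) = Φ[(d − 1.96·SE0)/SE1]

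**1. The plan's own power.** p1 = 0.11, p2 = 0.17, p̄ = 0.1589, SE0 = 0.02213, SE1 = 0.01970. Φ[(0.06 − 0.04337)/0.01970] = Φ(0.844) = 80.1%. The stated 80% is reproduced with the historical women counted at full weight.

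**2. Share of an era effect that passes through.** If all prospective women differ from historical women by e, the 74 concurrent controls share the shift. The apparent eCTG effect is then e × 1,400/1,474 = 0.95e.

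**3. No eCTG effect, prospective risk lower by e (assumed).** Worked for e = 4 points: p1 = 0.13; p2 = (1,400×0.17 + 74×0.13)/1,474 = 0.1680; d = 0.0380; SE0 = 0.02224; SE1 = 0.02080. Φ[(0.0380 − 0.0436)/0.02080] = Φ(−0.27) = 39.4%.

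| Drop e (points) | Apparent benefit (points) | P(significant benefit) |
|---|---|---|
| 1 | 0.95 | 5.9% |
| 2 | 1.9 | 12.5% |
| 3 | 2.85 | 23.6% |
| 4 | 3.8 | 39.4% |
| 6 | 5.7 | 76% |

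The nominal rate in this direction is 2.5%.

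**4. True 6-point effect, prospective risk higher by 2 points (assumed).** Concurrent CTG 19%, eCTG 13%, pooled controls (238 + 14.06)/1,474 = 17.1%, d = 0.041. Φ[(0.0410 − 0.0439)/0.02083] = Φ(−0.14) = 44.5%.

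**5. Does propensity adjustment change this?** A simulation of 600 runs per setting had no eCTG effect and the same covariate distribution in both eras. Logistic regression on a covariate-only score rejected in about 5%, 12%, 34% and 72% of runs for drops of 0, 2, 4 and 6 points. Adding an era term brought rejection back to 3–5%, but the eCTG effect then rests on the 74 concurrent controls.

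**6. What the concurrent controls can show (95% CI half-widths).**
- Concurrent v historical CTG: 1.96·√[0.1411(1/n + 1/1,400)], where 0.1411 = 0.17×0.83. This is 12.3 points for n = 37 and 8.8 for n = 74.
- eCTG v concurrent CTG: 1.96·√[0.11×0.89/335 + 0.1411/n]. This is 12.6 points for n = 37 and 9.2 for n = 74. Power for 17% v 11% is 22% and 32%.

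**The case against.** Historical controls are the declared design, the article acknowledges era differences, and it relies on sensitivity analyses as well as the score. Those analyses may be specified in an analysis plan that is not shown, so the lack of an era analysis in a condensed article is no fault. That stands. The covariate list is also open-ended, and medication use or length of stay might absorb a little practice change. What remains is the positive statement that the adjustment accounts for practice change, which the described method cannot deliver.

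Several stronger readings are tempting but not supported:
- **All of an era effect is read as an eCTG effect.** The concurrent controls share the new era, so the share is about 95%. The 74 is a planned count; sampled women for whom no device is free within 24 hours would add to it.
- **Trace review and an SOP were absent in 2014–2019.** The article does not say so. Their link to study start suggests they are new, but this is inference. The strengths and limitations box ties the SOP and daily review to eCTG traces, so they may partly belong to the intervention. The point is firmest for staff training.
- **COVID is a failed reason for ending the window in 2019.** The article says "numbers from MMC of 2020–2021 are not included in the sample size calculation". That concerns the assumed event rate. No reason is given for the window.
- **The window must be moved.** Women from 2022–2023 also precede the study's training, so the step at study start would remain. At 1,400/6 = 233 a year, dropping 2014–2015 loses about 467 women and adding January 2022 to the start of inclusion gains about 430, so the total would not hold.

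**Conclusion.** The point holds as a wrong claim about what the adjustment does. The score can balance measured case mix between the cohorts. It cannot separate eCTG from a change in risk at equal covariates, and about 95% of such a change enters the primary estimate.

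The size rests on assumed drifts. The article gives neither size nor direction, and a reader should not infer that a drift has been shown. Modest drifts matter all the same: 2 points downward raises the false-benefit rate from 2.5% to about 13%, and 2 points upward takes power from 80% to about 45%. The calculations also assume the planned counts, a 17% control risk, an absolute 6-point effect and no covariate differences between eras.

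The concurrent controls cannot settle the matter. Only 37 are randomly non-sampled, the other 37 being self-selected decliners, and the intervals are wider than the effect sought. As planned, a significant pooled difference could not by itself be attributed to eCTG.

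**What to change.** 1. **Correct the claim.** In Study limitations, delete the statement that propensity adjustment accounts for practice change. In Statistical analysis, limit the score's second task to measured case-mix differences between the cohorts. State that the pooled estimate compares eCTG plus the study's training and trace review with earlier care, and that a pooled difference alone will not be attributed to eCTG.
2. **Report two further comparisons beside the pooled result, with 95% CIs:** eCTG v concurrent CTG (the 37 non-sampled women, and all of about 74), and concurrent v historical CTG. Say in advance that they are imprecise (about ±12 or ±9 points), and that a non-significant concurrent-v-historical difference does not show that there was no drift.
3. **Add a sensitivity analysis for drift.** Show how large an era drift would overturn the pooled result, with the calendar-year trend among historical CTG women as a guide. For illustration, an observed 17% v 11% has a lower confidence limit of 6 − 1.96×1.97 = 2.1 points, so a downward drift of about 2.1/0.95 = 2.3 points would remove significance.

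The cost is a little more analysis, changes of wording and a more cautious conclusion. No further recruitment or record collection is needed. Changing the historical window is optional: it is a trade-off and does not remove the step at study start.
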